## 6.1 Principles

The primary endpoint is the by-arm rate of hospital admission or death between D0 and D14 (binary outcome in the primary analysis)

The primary endpoint analysis consists in multiple sub-analyses with multiple arms, multiple stages (sequential analyses) and procedures to manage randomisation treatment discontinuation or missing values. Tests multiplicity due to multiple stages will be managed by alpha spending function methods.

This trial is an adaptive phase III trial. Sequential analyses will be performed for the primary endpoint at D14 (and D28 for the last one) with different objectives:

- Interim analysis n°1: futility at D14
- Interim analysis n°2: futility at D14
- Interim analysis n°3: futility and early efficacy at D14
- Primary analysis: demonstrated efficacy at D14
- Sensibility analysis: maintained efficacy at D28

Each analysis on the primary endpoint will be on intention-to-treat with "missing as failure" (ITT-M=F).

Each experimental arm will be independently compared to the control arm, which leads to several paired tests.

Management of withdrawal or addition of an arm during trial:

- Arm withdrawal  
If an interim analysis demonstrates that it is useless to continue with an experimental arm compared to the control arm, this arm is discontinued and the trial continues with the other arms.

If an interim analysis demonstrates the early efficacy of an experimental arm compared to the control arm, this arm becomes the new control arm and the former control arm is discontinued. Either the SAB and the sponsor decide to definitively stop the trial, or a protocol amendment describes the implications regarding trial conception and statistical analysis, especially the comparison between the new control arm with the other arms.

- Arm addition

If a new medicine is deemed interesting after the trial started, a new arm is added. A protocol amendment describes the implications trial conception and statistical analysis, especially the comparison between the new arm with the control arm.

The primary analysis will be performed in the strata of participants not taking renin-angiotensin system blockers (ACEI or ARB) before inclusion, if the Telmisartan arm is maintained up to the end of the trial.

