### 1.4.1 Choice of study model

Preclinical and clinical data suggesting the effectiveness of drugs against SARS-CoV-2 are still limited. A trial launched in a context of emergency should be able to integrate those considered suitable under current knowledge, while allowing them to be discarded quickly, if they do not prove immediately promising. Drugs should be able to be included during the course of the trials if new promising evidence arise in the interim.

A multi-arm, multi-stage (MAMS) study would be more efficacious in this context than separated trials with two arms (experimental treatment vs. control). This type of trial, offering the opportunity to plan in advance to change one or several aspects of the trial, is particularly suited to the current, highly-evolving, scientific context. MAMS trials allow simultaneous comparison of a certain number of experimental treatments with a single control treatment. This type of

trial provides answers more rapidly and allows the abandonment of arms for futility over planned intermediate analyses or new scientific facts or even to add an arm over the course of the trial.

Three intermediate analyses are planned over the course of the trial, after recruiting 30, 60 and 102 participants per arm. They shall cause the halting of arms, should they prove futile or toxic. At the 3rd intermediate analysis, a preliminary efficacy analysis will allow identification of any treatment, which proves to be efficacious before the end of the trial. This treatment shall then become the standard. A halt on grounds of insufficient safety shall be possible at any point, subject to approval from the DSMB, without the need for a formal statistical criterion.

Multiple statistical tests shall be conducted on grounds of the multi-stage design and the existence of several arms. Type one alpha error shall not be adjusted on grounds of the absence of an objective to extend the indication. The objective is to identify all efficacious drugs and not to identify the best.

Overall, this type of model provides us with a concomitant optimisation of the evaluation of various therapeutic strategies, while adapting itself to the international scientific context and progressively evaluating the most promising strategy or strategies.

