
## 3 OBJECTIVES

### 3.1 Main objective

The study's main objective is to appraise the efficacy of several specific experimental treatments, compared with standard of care, to avoid hospitalisation or death on Day 14 among adults older than 65, suffering from symptomatic infection by SARS-CoV-2, presenting symptoms for fewer than 72 hours at the time of testing and having no hospitalisation criterion.

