## 6.2 Sample Size

### 6.2.1 Participants not taking ACEI or ARB before inclusion

The incidence assumptions on primary endpoint are based on extrapolations from aggregated data published in other contexts thus far. The DSMB will check these assumptions and recommend a sample size revision, if needed.

We assumed that the proportion of participants reaching the primary endpoint at D14 in the control arm could be up to 25%. An experimental treatment will be deemed efficient if this proportion is reduced by at least one half. We also considered a power of 80% for all tests.

Three futility (interim) analyses will be performed successively. We defined successive arm discontinuation thresholds for the one-way first type error alpha using STATA package NStageBin for conception and sample size of MAMS trials (65,66).

Two efficacy analyses (interim n°3 and primary) will be performed successively. We will use the O'Brien & Fleming procedure to define the first type error alpha for each analysis, based on the data observed at the first futility analyses (67,68).

Sensitivity analysis at D28 will be exploratory only, without impact on sample size.

Tests of difference between arms will be one-sided. Arm discontinuation thresholds and sample size for each analysis are given here below:

| Analysis    | Trigger
Number of participants in the control arm having reached D14 | Objectives     | Alpha           |
|-------------|-------------------------------------------------------------------------|----------------|-----------------|
| Interim n°1 | 30                                                                      | Futility       | 0,65            |
| Interim n°2 | 60                                                                      | Futility       | 0,45            |
| Interim n°3 | 102                                                                     | Futility       | 0,25            |
|             |                                                                         | Early efficacy | O'Brien-Fleming |
| Primary     | 169                                                                     | Efficacy       | O'Brien-Fleming |
| Sensitivity | End of trial                                                            | Efficacy       | 0,05            |

The sample size required is 169 participants by arm (845 overall). Since the "Missing as failure" procedure is used, there is no need to increase sample size to account for missing data.

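### Standard care closes at the first early success, and no test against standard care is kept for drugs still open, although the aim is to find every efficacious drug

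*Protocol*

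**What the plan says.** Protocol 6.1, under arm withdrawal, states that when an interim analysis shows early efficacy of an experimental arm, "this arm becomes the new control arm and the former control arm is discontinued". Two continuations are offered. The SAB and the sponsor may stop the trial for good, or a protocol amendment describes the consequences for design and analysis, in particular how the new control compares with the other arms. Section 1.4.1 agrees that the successful treatment becomes the standard.

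Section 1.4.1 also says: "The objective is to identify all efficacious drugs and not to identify the best". The main objective in 3.1 is to "appraise the efficacy of several specific experimental treatments, compared with standard of care, to avoid hospitalisation or death on Day 14". Sections 1.4 and 4.1 describe a superiority trial, and 6.2.1 adds: "Tests of difference between arms will be one-sided". Early efficacy is examined only at interim 3, for all arms at once.

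**The concern.** Once the control is replaced, the only comparison that 6.1 names is between the winner and the remaining arms. That asks which drug is better, the question 1.4.1 sets aside, and no longer asks whether each drug beats standard care, the question in 3.1. A drug that truly halves the event rate but has not yet crossed its boundary would have no stated route to being shown efficacious. The standard-care participants randomised alongside it, 102 or more, would have no stated role in its final analysis.

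Section 1.4.3 recognises this difficulty elsewhere. If hydroxychloroquine became the control, it says, an absence of difference would allow no conclusions. The same holds when the control is a drug just shown to work.

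Timing adds to the problem. The amendment would be written after the interim 3 results are known. Under 8.1 the SAB decides on protocol changes, and its members include the coordinating investigator, the senior statistician and a sponsor representative. The primary comparison for the open arms could therefore be chosen with knowledge of the data.

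**Working it through.** **Inputs from Protocol 6.2.1.** Control event rate 25%. Target effect: "An experimental treatment will be deemed efficient if this proportion is reduced by at least one half", so 12.5%. Power: "We also considered a power of 80% for all tests". Looks at 30, 60 and 102 per arm with one-sided futility levels 0.65, 0.45 and 0.25; final analysis at 169 per arm. Efficacy at 102 and 169: "We will use the O'Brien & Fleming procedure to define the first type error alpha for each analysis".

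**Assumptions.** The overall efficacy alpha is not stated, so one-sided 0.025 and 0.05 were both run. Also assumed: Lan-DeMets form of O'Brien-Fleming, binding futility rules, pooled z tests, and two effective arms A and B, both at 12.5%.

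**The plan's own figure.** n = [z(1−α)·√(2p̄q̄) + z(power)·√(p₁q₁ + p₂q₂)]² / (p₁ − p₂)², with p̄ = 0.1875, √(2p̄q̄) = 0.552, √(p₁q₁ + p₂q₂) = 0.545 and (p₁ − p₂)² = 0.015625.
- One-sided 0.025, 80% power: (1.960 × 0.552 + 0.842 × 0.545)² / 0.015625 gives 152, or 168 with continuity correction.
- One-sided 0.05, 90% power: (1.645 × 0.552 + 1.282 × 0.545)² / 0.015625 gives 166.

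Both are close to 169. At their stated alphas the three futility looks each have about 95% power, so the inputs are read correctly.

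**Early boundary.** Information fraction t = 102/169 = 0.604. Alpha spent is 2[1 − Φ(z(1−α/2)/√t)].
- α = 0.05: spends 0.0116; boundaries 2.27 (interim 3) and 1.68 (final).
- α = 0.025: spends 0.0039; boundaries 2.66 and 1.98.

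**What happens at interim 3** (simulation, 400,000 trials):

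| | α = 0.025 | α = 0.05 |
|---|---|---|
| A crosses | 36% | 51% |
| Given A crosses: B also crosses | 57% | 68% |
| Given A crosses: B open, not crossed | 40% | 28% |
| Given A crosses: B already stopped for futility | 3% | 4% |

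Exactly one of the two drugs crosses while the other stays open in 2 × 0.356 × 0.401 = 0.29 of trials (α = 0.025) and 2 × 0.511 × 0.283 = 0.29 (α = 0.05).

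**What then happens to the open, equally effective B:**

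| Test applied to B | α = 0.025 | α = 0.05 |
|---|---|---|
| Superiority over A, cumulative data at 169 | about 0% | 0.02% |
| Superiority over A, post-swap data only (67 per arm) | 2% | 5% |
| Against concurrent standard care, 102 per arm | 63% | 64% |
| Against concurrent standard care, 128 per arm | 75% | 78% |
| Against standard care kept to 169 | 87% | 89% |

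The 128 adds participants already randomised and awaiting D14: 169 × 14/90 ≈ 26 per arm, assuming even accrual over the planned 3 months. The 102 and 128 rows use the boundary planned for 169. A boundary recalculated for the smaller sample is slightly lower and raises these figures slightly.

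Given that A crosses, the overall chance of identifying B falls from 92% to 57% (α = 0.025) or from 93% to 68% (α = 0.05) if B must beat A on cumulative data rather than beat a control kept to 169.

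**The case against.** A reader might infer that, once one arm succeeds, any equally effective drug will almost surely be missed. The documents do not support this. All arms are tested at the same interim 3, and 57% to 68% of equally effective partners cross there too.

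A reader might also infer that 6.1 orders a superiority test against the winner. It does not. It fixes no hypothesis, test or dataset, it allows the trial to stop, and 4.2.2 says the DSMB is consulted urgently and the design adapted. A non-inferiority comparison, or use of the accrued control data, remains possible. The superiority label in 1.4 and 4.1 describes the original design. All of this stands, and it narrows the point. It does not remove it: the only comparison named is with the new control, no non-inferiority margin appears anywhere, and stopping the trial would also leave the open drug unproven.

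The strongest objection is to the remedy. Closure is triggered by a result that depends on the shared controls, so it favours trials with a high observed control rate. For a useless B (25%), given that A crossed, the false-positive rate is about 4.8% (α = 0.025) or 7.5% (α = 0.05), and within the open, uncrossed subset about 12% or 19% to 20%. This is true, but the inflation is conditional and comes mostly from sharing a control: with the full 169 controls the corresponding rates given A crossed are 4.7% and 7.0%. The unconditional one-sided error stays within nominal, at 2.3% and 4.5%.

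**Conclusion.** The point holds in limited form. Section 6.1 closes standard care at the first early success without saying how the remaining arms can still be shown better than standard care, which conflicts with 1.4.1 and 3.1. It matters for an equally effective drug still open but uncrossed at interim 3: 28% to 40% of such drugs given that another crosses, and about 29% of trials with two effective arms. A superiority test against the winner would succeed for that drug in about 0% to 5% of cases, against roughly 63% to 78% with concurrent standard-care participants. The sizes rest on the assumed alphas, the Lan-DeMets boundary, 25% versus 12.5%, and two effective arms.

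This goes beyond detail that can be left to the statistical analysis plan, because 6.1 itself sets the rule and names the comparison. It should be fixed before interim 3.

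**What to change.** State in 6.1 that, if the control is replaced or the trial stops at interim 3:
- the primary efficacy test of each arm still open remains the comparison with the original standard-care arm;
- it uses all participants of both arms randomised concurrently up to control closure, including those still awaiting D14;
- it is made at the final efficacy boundary, recalculated by the alpha-spending function for the information actually reached;
- the comparison with the new standard is secondary, and not beating it is not evidence of inefficacy.

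The cost is protocol wording and one further analysis. No extra patients are needed, and the time at which standard care closes does not change. The retained test has fewer controls than the planned 169, hence lower power than the 87% to 89% available with the control kept. Reports should acknowledge that, once a first arm has crossed early, the chance of a false positive in a second is raised to about 5% to 7.5%.

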## 6.2 Sample Size

### 6.2.1 Participants not taking ACEI or ARB before inclusion

The incidence assumptions on primary endpoint are based on extrapolations from aggregated data published in other contexts thus far. The DSMB will check these assumptions and recommend a sample size revision, if needed.

We assumed that the proportion of participants reaching the primary endpoint at D14 in the control arm could be up to 25%. An experimental treatment will be deemed efficient if this proportion is reduced by at least one half. We also considered a power of 80% for all tests.

Three futility (interim) analyses will be performed successively. We defined successive arm discontinuation thresholds for the one-way first type error alpha using STATA package NStageBin for conception and sample size of MAMS trials (65,66).

Two efficacy analyses (interim n°3 and primary) will be performed successively. We will use the O'Brien & Fleming procedure to define the first type error alpha for each analysis, based on the data observed at the first futility analyses (67,68).

Sensitivity analysis at D28 will be exploratory only, without impact on sample size.

Tests of difference between arms will be one-sided. Arm discontinuation thresholds and sample size for each analysis are given here below:

| Analysis    | Trigger
Number of participants in the control arm having reached D14 | Objectives     | Alpha           |
|-------------|-------------------------------------------------------------------------|----------------|-----------------|
| Interim n°1 | 30                                                                      | Futility       | 0,65            |
| Interim n°2 | 60                                                                      | Futility       | 0,45            |
| Interim n°3 | 102                                                                     | Futility       | 0,25            |
|             |                                                                         | Early efficacy | O'Brien-Fleming |
| Primary     | 169                                                                     | Efficacy       | O'Brien-Fleming |
| Sensitivity | End of trial                                                            | Efficacy       | 0,05            |

The sample size required is 169 participants by arm (845 overall). Since the "Missing as failure" procedure is used, there is no need to increase sample size to account for missing data.

This size may vary depending on the discontinuation or addition of arms during trial:

- If one arm is discontinued: from -67 participants (discontinuation at interim analysis n°3) to -139 participants (discontinuation at interim analysis n°1)
- If one arm is added: from +169 participants (addition at the time of first participant inclusion) to +338 participants (addition after the last planned inclusion).

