Weighting of values by estimated probability that a value is missing, obtained through modelling from baseline participants' characteristics and follow-up characteristics collected for all participants.

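### Missing-as-failure does not remove the need to allow for missing data: it costs power at 169 per arm, and neither a missing rate nor an overall efficacy alpha is stated

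*Protocol*

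**What the plan says.** Section 6.2.1 assumes that "the proportion of participants reaching the primary endpoint at D14 in the control arm could be up to 25" per cent, and adds: "An experimental treatment will be deemed efficient if this proportion is reduced by at least one half". On power it says "We also considered a power of 80% for all tests", and on direction "Tests of difference between arms will be one-sided". Futility looks at 30, 60 and 102 per arm use one-sided thresholds of 0.65, 0.45 and 0.25. Efficacy is tested at 102 and 169 per arm. For these tests the protocol says "We will use the O'Brien & Fleming procedure to define the first type error alpha for each analysis" but gives no total. The only 0.05 in the table is in the row for the exploratory D28 analysis. The section then concludes that "there is no need to increase sample size to account for missing data".

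Section 6 defines missing-as-failure as scoring any missing value as a failure. Section 6.1 applies it throughout: "Each analysis on the primary endpoint will be on intention-to-treat with" that rule, so the futility looks are included. Section 6 also lists a worst-case procedure in both directions and an inverse-probability procedure, the latter described as "Weighting of values by estimated probability that a value is missing". Section 6.3.4 makes both of these secondary analyses of the primary endpoint.

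**The concern.** The sentence treats a full denominator as if it were full information. A participant whose outcome is unknown and who is counted as a failure contributes noise that is the same in both arms. The difference between the arms shrinks, and both rates move towards 50%, where the variance is larger. The stated power therefore describes a trial with complete D14 data. If missingness differs between the arms, which is plausible in an open-label trial against a food supplement, the same rule creates a difference that the drug did not cause. Separately, the inverse-probability entry as worded gives most weight to the participants most likely to be missing, without the inversion that its name promises.

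**Working it through.** **Inputs from section 6.2.1:** p_C = 0.25, p_E = 0.125, difference d = 0.125, 169 per arm, one-sided tests, looks at 30/60/102/169. **Assumptions:** total efficacy alpha of one-sided 0.025 or 0.05; missing rate m equal in both arms and unrelated to outcome; binding futility; O'Brien-Fleming boundaries at 102 and 169.

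**Reproducing the plan.**
- Single look: n = [z_α√(2p̄(1−p̄)) + z_β√(p_C(1−p_C)+p_E(1−p_E))]²/d². With p̄ = 0.1875, α = 0.025 and 80% power this is (1.960×0.5520 + 0.842×0.5449)²/0.015625 = 152, or 168 with continuity correction, against the stated 169. At α = 0.05 it gives 120 and 136.
- Stage formula: n = (z_α + z_power)² × 0.296875/0.015625 = 19(z_α + z_power)². At 95% stage power, α = 0.65, 0.45 and 0.25 give 30.1, 59.6 and 102.2, matching 30, 60 and 102. For the last stage, α = 0.025 at 85% power gives 170.6, and α = 0.045 at 90% power gives 168.4.
- So 169 is compatible with more than one alpha, and both ends of the range are carried forward.

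**Effect of the rule.** Each analysed rate becomes q = m + (1 − m)p, so the difference is (1 − m)d. At m = 0.05:
- q_C = 0.05 + 0.95×0.25 = 0.2875 and q_E = 0.05 + 0.95×0.125 = 0.16875;
- the difference is 0.11875 instead of 0.125;
- the variance sum is 0.3451 instead of 0.2969.

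**Power at 169 per arm** (four-stage figures by simulation; single look uncorrected):

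| Missing, each arm | Four-stage, 0.025 | Four-stage, 0.05 | Single look, 0.025 | Single look, 0.05 |
|---|---|---|---|---|
| 0% | 80% | 85% | 84.1% | 90.6% |
| 2% | 76% | 82% | 80.1% | 87.8% |
| 5% | 70% | 77% | 74.2% | 83.3% |
| 10% | 60% | 68–69% | 64.7% | 75.6% |

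A multivariate normal calculation of the four-stage design agrees to about one point (79.3%, 69.0% and 59.5% at 0.025 for 0%, 5% and 10%).

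**Against simply dropping the missing.** With 169 × 0.95 = 160.55 per arm and undiluted rates, single-look power at 0.025 is 82.2%, compared with 74.2% under missing-as-failure.

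**Unequal missingness.** With no drug effect (25% in both arms), four-stage, simulated:

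| Missing, control / experimental | Type I error, 0.05 | Type I error, 0.025 |
|---|---|---|
| 0% / 0% | about 4% | about 2% |
| 6% / 4% | 7–8% | about 4% |
| 10% / 5% | 15–16% | about 10% |
| 5% / 10% | 0.7% | 0.3% |

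**The weight.** Invented illustration: 80% of participants have 10% risk and 5% missing; 20% have 40% risk and 30% missing. The true rate is 0.8×0.10 + 0.2×0.40 = 16.0%. Weighting observed values by P(missing) gives (0.0038 + 0.0168)/(0.038 + 0.042) = 25.8%. Weighting by 1/P(missing) gives 10.9%. Weighting by 1/P(observed) returns 16.0%.

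**The case against.** **Follow-up is close and missingness may be small.** There are contacts on D1, 3, 5, 7, 9, 12 and 14, and the mobile team is activated when a remote contact fails (5.3.5). Home visits may be replaced only for people who can be reached by telephone (5.3.9). This makes 10% missing, and a 10% versus 5% imbalance, look high. The point stands, and it is why the smaller 6% versus 4% case is shown. It does not make the sentence true: at one-sided 0.025 even 2% missing gives 76% four-stage power.

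**A reader might infer that 5% missing always breaks the stated 80%.** The documents do not support that without conditions. The 80% is claimed for all tests and can be read test by test. A single-look uncorrected final test at 0.045 to 0.05 keeps 82–83% at 5% missing. That reading starts from about 90% with complete data, however, and it leaves out the power lost at the futility looks.

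**The loss depends on who is missing.** If every missing participant would have had the event, nothing is lost. If only non-events go missing, adding 5 points to each arm, four-stage power is still 72% (0.025) or 79% (0.05).

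**Other safeguards exist.** The two-direction worst-case analysis addresses unequal missingness, but it is secondary. It can expose a fragile result; it does not change the error rate of the primary test or the arm-dropping decisions. The DSMB may recommend a new sample size, but section 6.2.1 ties this to the incidence assumptions.

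**A reader might also infer that missing-as-failure must be replaced, or that the inverse-probability analysis is invalid.** Neither follows. The choice of primary rule is a trade-off for the sponsor. The procedure's own name suggests that the weight is a wording slip, in one secondary analysis whose details are left to the SAP.

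**Conclusion.** The sentence in section 6.2.1 is false and should be fixed. With equal missingness unrelated to outcome, overall four-stage power at 169 per arm is about 80% (one-sided 0.025) to 85% (0.05) with complete data, 70–77% at 5% missing and 60–69% at 10%. The loss exceeds that from dropping the missing cases. Type I error also depends on the balance of missingness, rising at one-sided 0.05 from about 4% to 7–8% at 6% versus 4% missing and to about 16% at 10% versus 5%. All of these figures rest on missing rates and a total alpha that the protocol does not give, so they are a range and not a single corrected value. The weight in the inverse-probability entry is wrong as worded, but this is minor.

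**What to change.** 1. In section 6.2.1, delete the sentence on missing data. State the overall one-sided efficacy alpha and an expected D14 missing rate, and restate power under missing-as-failure as a range around that rate, saying whether it is per test or over all four stages.
2. In section 6, redefine the inverse-probability weight so that observed values are weighted by 1/P(outcome observed).

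Both are changes of wording and need no extra patients. The cost is that the stated power becomes less favourable. If the sponsor chose instead to hold 80% four-stage power at 5% missing, that would take about 190 (0.05) to 221 (0.025) per arm; this is information for that decision and not part of the correction.
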